### 11.3.2 Analysis Plan

### 11.3.2.1 Baseline Data

Baseline characteristics will be summarized and described in a frequency list.

### 11.3.2.2 Analysis of Efficacy

The definition of efficacy endpoints has been detailed in previous section. Cumulative incidence of relapse post-transplantation is calculated by accounting for competing risk. Non-relapse mortality is considered a competing risk for relapse. The comparison of the cumulative incidence of relapse is tested using Fine and Gray model. OS and LFS are estimated using the Kaplan-Meier method and compared using the log-rank test. The corresponding HR and 95% CI were estimated using the Cox proportional hazards model. All statistical tests are two-tailed with a significance level of 0.05. SPSS 20.0 (SPSS Inc., Chicago, IL, USA) and R version 3.3.0 (R Development Core Team, Vienna, Austria) are used for all data analysis.

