## 5.2 Treatment Allocation and Blinding

This is an open-label study. Neither subjects nor investigators will be blinded to treatment. Upon completion of all the required screening assessments, eligible subjects will be randomized at 1:1 ratio to receive sorafenib maintenance or non-maintenance post-transplantation. Randomization is done with permuted blocks (block size four), and implemented through an interactive web-based response system.

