## 6.4 Schedule and methods of Efficacy Assessments

Disease assessment including routine blood and BM assessment will be regularly performed post-transplantation. Routine blood is monitored before randomization, twice a week for the first month after enrollment, once a week from the 2nd to 3rd month after enrollment, and then once every two weeks until the study is completed. BM assessment, including BM smear and FLT3-ITD mutation is performed before randomization, every month for the first three months after enrollment, every two months from the 4th to 9th month after enrollment, and then every three months until the study is completed. Mutation analysis of the FLT3-ITD (exons 14 and 15) gene is performed by polymerase chain reaction and direct sequencing. All subjects who complete treatment or withdraw from the study must receive efficacy assessment.

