### 11.2.1 Sample Size Assumptions

The sample size calculation is based on the primary endpoint, the 1-year cumulative incidence of relapse post-transplantation, with the following assumptions:

- - - - the 1-year cumulative incidence of relapse in the control group: 40%
      - the 1-year cumulative incidence of relapse in the sorafenib group: 20%
      - a 1:1 randomization scheme
      - a 5% one-tailed risk of erroneously claiming a difference in the presence of no true underlying difference by z-test with pooled variance
      - a 90% chance of successfully declaring a difference in the presence of a true underlying difference (power)
      - 10% percent of cases drop

Under the above assumptions, a total sample size of 194 subjects is required (97 in each group).

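### Adding the pre-randomization marrow FLT3-ITD result to the primary Fine and Gray model is a cheap improvement, worth about 0 to 7 points of power

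*Protocol*

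**What the plan says.** Section 11.3.2.2 (Analysis of Efficacy) fixes the family of the primary test: "The comparison of the cumulative incidence of relapse is tested using Fine and Gray model". It also fixes the competing event ("Non-relapse mortality is considered a competing risk for relapse") and the error level ("All statistical tests are two-tailed with a significance level of 0.05"). It does not say what enters the model besides treatment. The statistical analysis row of the Synopsis repeats the test in the same terms.

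Section 5.2 describes permuted blocks of four and names no stratification factor.

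Section 6.4 states: "BM assessment, including BM smear and FLT3-ITD mutation is performed before randomization". Section 3 and Section 5.4 carry the same schedule. Section 6.4 gives the assay as polymerase chain reaction with direct sequencing. Under Section 4.1.2, every subject must be in composite complete remission, confirmed by marrow analysis within 3 days before randomization.

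**The concern.** Neither the randomization nor the stated analysis takes account of any prognostic factor, in a trial of about 194 patients. A chance imbalance in a strong predictor of relapse would then pass straight into the primary comparison, and variation that a baseline covariate could explain is left in the error.

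Residual FLT3-ITD in the marrow is a natural candidate. It is the target of the study drug. Section 1 links FLT3-ITD disease to higher relapse and treats its inhibition as a way to prevent relapse. The result is scheduled before randomization, so it cannot be affected by treatment. At stake are a few points of power, some protection against imbalance, and a covariate choice fixed before outcomes are seen. The last matters in an open-label trial, where a later choice could look driven by the data.

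**Working it through.** **1. The plan's own figure.** Inputs from Section 11.2.1: 40% versus 20% at 1 year, 1:1, 90% power, and "a 5% one-tailed risk of erroneously claiming a difference in the presence of no true underlying difference by z-test with pooled variance".

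n per group = [z(1-α)·√(2·p̄·(1-p̄)) + z(0.90)·√(p₁(1-p₁) + p₂(1-p₂))]² / (p₁-p₂)², with p̄ = 0.30.

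= [1.645·√0.42 + 1.282·√0.40]² / 0.04 = [1.066 + 0.811]² / 0.04 ≈ 88.03.

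Strictly this rounds up to 89, but 88 gives 89.99% power, so the plan's 88 reproduces. The planned 97 follows from 88 × 1.10 = 96.8.

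**2. Power of the stated two-tailed test, no covariate.** Power = Φ[(0.20·√n - 1.960·√0.42)/√0.40].

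- n = 88: Φ[(1.876 - 1.270)/0.632] = Φ(0.958) = 83.1%
- n = 97: Φ[(1.970 - 1.270)/0.632] = Φ(1.106) = 86.6%

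The implied subdistribution hazard ratio (SHR) is ln(0.8)/ln(0.6) = 0.437. Schoenfeld's formula with 88 × 0.6 = 52.8 events gives 85.3%, and with 58.2 events (97 per group) 88.5%.

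**3. What adjustment adds.** This was simulated with 2,500 trials per scenario, each trial analysed both ways with a two-sided 0.05 Wald test of treatment. Patients who die without relapse stay in the risk set to 1 year; with censoring only at 1 year, that is the Fine and Gray risk set.

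Within each arm, P(no relapse by 1 year) = exp(-L·SHR^marker). L is solved so that (1-π)·exp(-L) + π·exp(-L·SHR) equals 0.6 (control) or 0.8 (sorafenib), where π is the share positive. For example, π = 20% and SHR 3 give L ≈ 0.395 and 0.165, a conditional treatment SHR of 0.418. The marginal incidences therefore stay at 40% and 20% in every scenario.

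π and the marker's SHR are assumptions, because the protocol gives neither. Gain in power (points), 88 per group / 97 per group:

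| Share positive | SHR 2 | SHR 3 | SHR 5 |
|---|---|---|---|
| 5% | 0.6 / 0.4 | 1.1 / 0.5 | 2.6 / 2.7 |
| 10% | 0.1 / 0.6 | 2.4 / 2.1 | 6.0 / 4.4 |
| 20% | 1.2 / 1.5 | 3.4 / 2.7 | 6.9 / 5.2 |
| 30% | 2.1 / 1.7 | 3.2 / 3.1 | 5.9 / 7.1 |

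At SHR 1.5 the gain over the same prevalences is 0 to 0.8. Simulation error on each power is √(0.84 × 0.16/2500) ≈ 0.7 points, which explains the uneven steps. Further runs at 88 per group (2,000 to 4,000 trials per scenario) agree: 0 to 1.3 points at 3-5% positive with SHR 2-3, and up to 7.5 at 20-30% with SHR 5. For a marker with SHR 1, power changed by no more than 0.4 points.

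**4. Effect on the estimate.** Across the table, the conditional treatment SHR runs from 0.389 to 0.435, against 0.437 marginal.

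**The case against.** The strongest reply is that nothing here is wrong. Section 11.3.2.2 neither declares the model unadjusted nor rules out covariates, and a covariate list is commonly left to a statistical analysis plan, which is not shown. An unadjusted two-arm comparison is valid under randomization. That stands, and it is why the point is only a suggestion. A reader might infer that the plan overlooks the marker or that its primary test is flawed; silence on covariates supports neither.

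The size also rests on inputs outside the protocol. Because everyone is in composite complete remission, positives may be few, and the low end of the gain cannot be told from zero. That stands as well: a guaranteed gain of even 1 point cannot be claimed. Unknown prevalence and strength set the size of the gain, however; no scenario showed a material loss.

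Nor is the change free. The hazard ratio becomes conditional, whereas the hypotheses in Section 11.1 concern incidence by arm. A small positive group makes the coefficient unstable. The test is scheduled, but no section makes an available result a condition of randomization, so some results may be missing.

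Finally, a drug aimed at the marker may work differently by marker status. The simulation assumes one treatment effect for both groups, so the gain is untested where effects differ.

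**Conclusion.** The point holds as a minor improvement. The protocol names no covariate and no stratification factor although a baseline marrow FLT3-ITD result is scheduled for everyone. Adjusting for it would add about 0 to 7 points of power at two-tailed 0.05, assuming 3-30% positive and a marker SHR of 2-5. The upper end needs a common and very strong marker (20-30% positive, SHR about 5). With rare positives and an SHR of 3 or less, the gain is about 0 to 1 point.

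A reader might also infer that adjustment restores the intended 90% power. The documents do not support that. The fall from 90% to about 83% at 88 per group comes from sizing the trial one-tailed (Section 11.2.1) and testing two-tailed (Section 11.3.2.2). That is a separate mismatch, and it needs its own resolution.

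**What to change.** Unless a statistical analysis plan already does so, amend Section 11.3.2.2, before any comparison of outcomes, to state:

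- The primary Fine and Gray model contains treatment and pre-randomization marrow FLT3-ITD status (positive/negative).
- The covariate is dropped if the pooled number of positives, counted without reference to arm or outcome, is below a stated minimum. Ten would be a workable choice: it is about 5% of 194 (0.05 × 194 = 9.7), the region where the gain at SHR 3 or less is about 1 point at most.
- A missing result is handled by a rule that keeps every randomized subject, for instance assignment to the more common category regardless of arm and outcome.
- The unadjusted Fine and Gray model is reported as supportive, beside the cumulative incidence of relapse by arm at 1 year.

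The cost is a few lines of text and no additional tests or visits. The primary subdistribution hazard ratio must then be described as conditional on baseline FLT3-ITD status.

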### 11.3.2.3 Analysis of Safety

Safety and tolerability will be assessed by incidence and severity of AEs and changes from baseline of all relevant parameters, including laboratory test values, physical examination, vital signs, and ECOG performance scores. The definition of AEs has been detailed in previous section. With the exception of GVHD and hematologic AEs, all AEs are graded according to CTCAE version 4.0. aGVHD, cGVHD, and hematologic AEs are graded as AEs according to our self-defined criteria. All subjects will be monitored for AEs within 210 days post-transplantation. Categorical data will be summarized by proportion of total subjects. Quantitative data will be described using arithmetic average or median for central tendency and standard deviation or interquartile range for distribution range.

# 12. Materials for the Study

All materials provided to study sites and investigators are as follows:

- The study protocol
- Informed consent
- CRF

# 13. Ethical Considerations

## 13.1 Responsibility of Investigators

The investigators have the responsibility for guarantee of the clinical study’s compliance with the protocol, Chinese good clinical practice (GCP) guidelines and applicable laws and regulations.

## 13.2 Informed Consent Process

Prior to participation in the study, subjects must be informed about objectives, methods, possible benefits, potential risks and possible discomforts of the study by investigators. They also should be informed that participation in the study would be voluntary, they can withdraw from the study at any time, there is no impact on the treatment of the disease whether they take part in the study and their privacy will be protected.

Subjects or their legally acceptable representative should have enough time to read the inform consent and raise queries. Written informed consent must be obtained from each subject, or their legally acceptable representative.

## 13.3 Good Clinical Practice

This study will be conducted in accordance with the Declaration of Helsinki and Chinese GCP. The study will be conducted only if it is approved by the ethical review committee of the principal study site. The investigators will guarantee that the study will be conducted in accordance with applicable laws and regulations, scientific and ethical principles of the People’s Republic of China. If the protocol needs revision during the study, the revised version must be reapproved by the ethical review committee of the principal study site. If new data related to study treatment are discovered, the informed consent must be revised and the revision must be reapproved by the ethical review committee of the principal study site and subjects.

## 13.4 Protection of Subjects’ Personal Data

Data collected in the study are limited to the efficacy and safety related to study treatment. Data will be collected and used in accordance with applicable laws and regulations.

# 14. Administrative Requirements

Neither the investigator nor the applicant can revise the protocol without agreement of the opposite side. All revisions of the protocol must be released by the applicant institution. To insure the integrity, accuracy and reliability of the data, relevant results of examination and treatment must be documented in original medical record and CRF. Independent clinical monitoring is performed regularly by a panel of qualified and experienced study investigators composed of hematologists who are blinded as to the treatment assignments.

# 16 Appendices

## 16.1 Appendix 1 Diagnosis and Classification of aGVHD and cGVHD

**Grading of aGVHD**

| Grade | Degree of organ involvement |
| --- | --- |
| I | Stage 1-2 skin rash; no gut involvement; no liver involvement; no decrease in clinical performance |
| II | Stage 1-3 skin rash; stage 1 gut involvement or stage 1 liver involvement (or both); mild decrease in clinical performance |
| III | Stage 2-3 skin rash; stage 2-3 gut involvement or 2-4 liver involvement (or both); marked decrease in clinical performance |
| IV | Similar to Grade III with stage 2-4 organ involvement and extreme decrease in clinical performance |

**Grading of cGVHD**

| NIH Global Severity of chronic GVHD |
| --- |
| Mild chronic GVHD |
| 1 or 2 Organs involved with no more than score 1 plus Lung score 0 |
| Moderate chronic GVHD |
| 3 or More organs involved with no more than score 1 |
| OR |
| At least 1 organ (not lung) with a score of 2 |
| OR |
| Lung score 1 |
| Severe chronic GVHD |
| At least 1 organ with a score of 3 |
| OR |
| Lung score of 2 or 3 |
| Key points:  In skin: higher of the 2 scores to be used for calculating global severity.  In lung: FEV1 is used instead of clinical score for calculating global severity.  If the entire abnormality in an organ is noted to be unequivocally explained by a non-GVHD documented cause, that organ is not included for calculation of the global severity.  If the abnormality in an organ is attributed to multifactorial causes (GVHD plus other causes), the scored organ will be used for calculation of the global severity regardless of the contributing causes (no downgrading of organ severity score). |


[figure not shown]

Figure 1. Organ scoring of chronic GVHD. ECOG indicates Eastern Cooperative Oncology Group; KPS, Karnofsky Performance Status; LPS, Lansky Performance Status; BSA, body surface area; ADL, activities of daily living; LFTs, liver function tests; AP, alkaline phosphatase; ALT, alanine aminotransferase; ULN, normal upper limit. *Weight loss within 3 months. †Skin scoring should use both percentage of BSA involved by disease signs and the cutaneous features scales. When a discrepancy exists between the percentage of total body surface (BSA) score and the skin feature score, OR if superfificial sclerotic features are present (Score 2), but there is impaired mobility or ulceration (Score 3), the higher level should be used for the final skin scoring. **Lung scoring should be performed using both the symptoms and FEV1 scores whenever possible. FEV1 should be used in the final lung scoring where there is discrepancy between symptoms and FEV1 scores.

[figure not shown]

Figure 1. (continued).

[figure not shown]

Figure 1. (continued).


## 16.2 Appendix 2

**ECOG Performance Status**

| **Grade** | **ECOG** |
| --- | --- |
| **0** | Fully active, able to carry on all pre-disease performance without restriction |
| **1** | Restricted in physically strenuous activity but ambulatory and able to carry out work of a light or sedentary nature, e.g., light house work, office work |
| **2** | Ambulatory and capable of all selfcare but unable to carry out any work activities. Up and about more than 50% of waking hours |
| **3** | Capable of only limited selfcare, confined to bed or chair more than 50% of waking hours |
| **4** | Completely disabled. Cannot carry on any selfcare. Totally confined to bed or chair |
| **5** | Dead |

